### Process evaluation analysis

Older adults purposively selected to participate in the process evaluation component of the trial, will be invited to participate in interviews designed to elicit *in-depth* information about the quality of processes embedded within the programs [68]. This component of intervention evaluation will draw from a qualitative *social constructionist* perspective [69] to understand in the older adults’ own words, the beneficial features and any problematic components of the exercise program. Social constructionism is concerned with understanding the manner in which people reflect on and interpret their own and others’ behaviors, and the meanings and values that they ascribe to those interactions. Data collected via the semi-structured interviews will be analyzed through use of inductive content analytic procedures [70], and themes will be identified that correspond to the strengths and limitations of the respective programs.

#### Trial status

In accordance with the proposed time-line, the full program (e.g., recruitment, randomization, baseline testing, six-month physical activity programs, post testing) has been completed for the first cohort of the GOAL Trial. For the second cohort, participants have also been recruited, randomized, and completed baseline measures. Currently, the second cohort of the trial is underway, but (at the time of this protocol manuscript submission) has not yet been completed). No data from either cohort have been subject to any form of data analysis.

## Discussion

Understanding the predictors of physical activity adherence is an important research endeavor within the fields of preventive medicine and health psychology. A growing body of epidemiologic evidence now exists in support of the ongoing involvement in active lifestyles among older adults, and indeed the benefits of regular activity among this population have been well-established [71]. Our proposed study will examine whether a theory-driven, evidence-based intervention has the capacity to support the sustained involvement in physical activity among older adults. The proposed research will also provide the most rigorous test to date of the efficacy of SASG physical activity settings for sustaining the physical activity behaviors of older adults. Although our previous research on exercise preferences [16, 19] as well as the predictive utility of intra-group similarity [16, 18, 20] points to the importance and viability of SASG group contexts for sustaining physical activity adherence behaviors, it should also be noted that these studies utilized non-experimental observational designs. Thus, the causal link between intra-group similarity and exercise adherence has yet to be examined.

In the current study, an experimental (RCT) design is used to examine the efficacy of SASG (and SAMG) settings, the findings of which have the potential to inform the delivery of effective health-enhancing physical activity interventions that are likely to sustain the adherence behaviors of older adults in those programs. If either the SASG or SAMG conditions have significantly higher adherence rates, when compared to the MAMG group, we will have preliminary evidence to support a *small change with substantive impact*. From a knowledge translation perspective, attending to group composition considerations is an easy, sustainable, and low-cost way to influence physical activity behaviors for older adults. This program would easily translate to a variety of physical activity settings including YMCAs, other community-centers, retirement communities, among others. The data collected in this trial have the potential to inform next steps for large-scale implementation and understanding potential mechanisms related to the efficacy of group-based interventions.

There are a few potential limitations to address at the onset. First, the MAMG is unique in that participants can choose any 3-day per week class offered at the YMCA. From a design perspective, there may be a limitation in giving MAMG participants choice in terms of which YMCA course they wished to participate, since participants in the SASG and SAMG conditions were not given any such choice. However, from a pragmatic perspective, we believe that the MAMG group represents the most appropriate type of control condition as it reflects the typical type of exercise class available within community exercise settings. Thus, MAMG provides a strong point of comparison.

There may also be critique of variation related to class leaders. Measures were taken in the extensive training of the volunteer, similar-aged instructors. All volunteer leaders were trained at the same time, through the three modules outlined above. In this way, we sought to increase the likelihood of treatment fidelity across all conditions at each site. However, there may be some inherent differences based on instructor personalities, level of exercise instructor experience, and so forth. To account for these potential differences across conditions and sites, the process evaluation includes queries about perceptions of the class leaders (e.g., leadership and communication style).

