**Discussion:**

Results from this trial will inform intervention designs to improve the exercise adherence behaviors of older adult. At a systems-level, should support be derived for the efficacy of the interventions tested in this trial, changing group composition (i.e., age, gender) represents a feasible program adaptation for physical activity centers.

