**Fig. 1 Fig1:**
[figure not shown]
Flow of participants through the trial

The design of the SASG physical activity condition was informed by the tenets of self-categorization theory as well as the results of a recent case study of a highly efficacious physical activity program entitled the *Lively Lads* (a pseudonym) for older adult males [22]. Although the *Lively Lads* program was developed by-seniors-for*-*seniors, it made use of a number of salient theory-driven group dynamics strategies that appear to be implicated in its success. Several of the *Lively Lads* strategies were utilized in the design of the SASG intervention arm of the GOAL Trial. First, one of the core features of this condition is that it designed exclusively for those of a similar age and same gender. Such an environment was reported by Dunlop and Beauchamp [22] to provide opportunities for social connectedness, as well as personal comfort (e.g., reduced likelihood of embarrassment and displays of physical incompetence in front of women). Second, the volunteer exercise class instructors are drawn from the ranks of older adults. Such an approach is consistent with research from the perspective of social cognitive theory, highlighting the value of ‘similar models’ as sources of vicarious efficacy enhancement information and verbal persuasion [40]. From the perspective of program sustainability, volunteer exercise leaders enable the program to keep its costs low (there are no costs involved in paying instructors, as they are volunteers). Consistent with social identity and self-categorization perspectives, the program also makes use of a series of strategies to foster group identity (e.g., providing participants with T-shirts to foster a sense of ‘distinctiveness’). Finally, although a major objective of the SASG intervention condition is to engage in physical activity, an important strategy (informed by both social identity theory and the *Lively Lads* program) is to provide opportunities for the older adults to connect with one another after the classes have ended (e.g., post-workout coffee gatherings). Although the *Lively Lads* program was developed with older adult males, classes are also provided in the GOAL Trial for older adult women at each YMCA site.

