The SAMG physical activity condition mirrors the SASG group condition, insofar as the program was restricted to older adults (≥65 years), but was open to older adults from both genders. The same strategies to those used within the SASG condition were also utilized (e.g., T-shirts, opportunities to socialize after the program), with classes also offered on three days per week. Older adults were also recruited to be instructors for the group classes (≥65 years), with both males and females invited to occupy these instructional roles.

The control condition operationalized within the RCT is designed to reflect ‘standard’ group-based exercises that one sees in typical physical activity centers. Specifically, these classes (regular group-based physical activity classes run by the respective YMCAs) are not restricted to participants on the basis of age or gender, and as such older adults in this condition participate in groups comprised of people younger than themselves as well as those of both genders. Specifically, participants randomized to this condition were invited to select one of the standard group-based exercise classes offered by the respective YMCA. Although these classes involve both GOAL Trial participants and regular YMCA members, only the older adults recruited to and consented in the GOAL Trial will be used in the analyses.

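### A difference from MAMG cannot be credited to group composition, because SASG and SAMG also carry a package of other features described only for those two arms

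*Protocol article*

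**What the plan says.** The Discussion ties the interpretation to the control comparison: "If either the SASG or SAMG conditions have significantly higher adherence rates, when compared to the MAMG group, we will have preliminary evidence" of a small change with a large impact. The next sentence names the lever, without qualification: "attending to group composition considerations is an easy, sustainable, and low-cost way to influence physical activity behaviors". The Discussion paragraph of the Abstract makes the same step. If the interventions prove efficacious, "changing group composition (i.e., age, gender) represents a feasible program adaptation for physical activity centers".

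The Study interventions section describes what each arm receives. In SASG, "the volunteer exercise class instructors are drawn from the ranks of older adults". Group identity is built by "providing participants with T-shirts to foster a sense of ‘distinctiveness", and members are given occasions to meet over coffee after class. For SAMG, "The same strategies to those used within the SASG condition were also utilized (e.g., T-shirts, opportunities to socialize after the program" and so on, and "Older adults were also recruited to be instructors for the group classes". Under Program structure, the intervention classes have bought-in playlists, a tutorial website, three instructor training modules with up to 45 hours available, and six recommended exercise sequences. The tailoring module refers only to SASG and SAMG.

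Of the control arm the article says that "these classes (regular group-based physical activity classes run by the respective YMCAs) are not restricted to participants on the basis of age or gender". MAMG participants choose one of these classes. The limitations in the Discussion acknowledge that choice and possible variation between class leaders. They do not mention the T-shirts, the gatherings, peer leadership as such, or the purpose-built content.

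**The concern.** The Abstract and Discussion present the trial as the first experimental test of whether similarity within a group affects adherence. A test of that claim needs arms that differ in composition and in little else. Here, moving from MAMG to either experimental arm changes age composition together with who leads the class, how group identity is fostered, whether socialising is organised, what is taught, and whether the participant chose the class.

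A centre acting on the stated conclusion would regroup its classes by age and perhaps gender. It would not thereby deliver what was tested. Even the low-cost argument draws partly on the package, since Study interventions attributes low running cost to the use of volunteer leaders. A positive result against MAMG could therefore be taken as evidence for age matching when some or all of it came from the other features.

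**Working it through.** **Step 1: set the arms side by side.** Sources are Study interventions, Program structure and the limitations paragraphs of the Discussion.

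| Feature | SASG | SAMG | MAMG |
|---|---|---|---|
| Group restricted to age 65 or over (*a*) | yes | yes | no |
| Single gender (*g*) | yes | no | no |
| Trained older volunteer instructors (*p*) | yes | yes | not described |
| T-shirts (*t*) | yes | yes | not described |
| Organised socialising (*s*) | yes | yes | not described |
| Trial-built class content (*c*) | yes | yes | regular YMCA classes |
| No choice of class (*k*) | yes | yes | choice given |

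**Step 2: write the arm means.** Assume additive effects, and read *not described* as absent. With *m* as the MAMG mean:

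- MAMG = *m*
- SAMG = *m + a + p + t + s + c + k*
- SASG = *m + a + p + t + s + c + k + g*

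The contrasts are then:

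- SAMG − MAMG = *a + p + t + s + c + k*
- SASG − MAMG = *a + p + t + s + c + k + g*
- SASG − SAMG = *g*

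The arm-by-term matrix has 3 rows, 8 columns (intercept plus seven features) and rank 3. Among the features only *g* is estimable. The six features *a, p, t, s, c, k* have identical columns, so only their sum can be estimated.

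**Step 3: relax the assumptions.**

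- Suppose one feature, such as socialising, was present in MAMG classes too. Then *s* drops out of the sum, but *a* stays tied to the rest. If it was present in some MAMG classes only, that variation comes from participants' own choice of class and is not a randomised comparison.
- Suppose SASG and SAMG also differ in tailoring (*d*) or instructor gender (*h*). Program structure says instructors learned to adapt the programme to their arm, and Study interventions says both men and women were invited to lead SAMG classes. Then SASG − SAMG = *g + d + h*, and even the gender-composition effect is isolated only if *d* and *h* are negligible.

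**Step 4: check that sample size is not the issue.** The Sample size section gives f = .25, alpha .05, power .80 and N = 211. With the noncentral F distribution and λ = N × f²:

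- N = 211: λ = 211 × 0.0625 = 13.19. With 5 numerator degrees of freedom (all six gender-by-condition cells), power is 0.8003, so the stated 211 is reproduced.
- After 25% attrition, 540 × 0.75 = 405 remain: λ = 405 × 0.0625 = 25.31. With 2 numerator degrees of freedom (condition), power is 0.997.

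The condition effect is well powered on these inputs. Step 2 does not involve N, so more participants would not separate *a* from the other terms.

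**The case against.** The strongest reply is that the article already presents the trial as a comparison of programmes. The Abstract speaks of two exercise programmes against a standard one, Hypothesis 1 is worded in terms of conditions, and the components are openly described. The sentence at issue is a knowledge-translation remark and not an analysis rule. The sentence before it claims only preliminary evidence, and the Abstract's version is conditional on success. MAMG is a defended pragmatic control. The Process evaluation section plans interviews, 15 per condition, that ask about subcomponents, including composition and the instructor.

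Much of this stands. The package comparison with MAMG is legitimate and useful, no test or sample size changes, and class choice is already disclosed. It does not remove the point. The sentence naming composition as the lever carries no hedge, the limitations omit most of the package, and interviews cannot apportion a difference in attendance.

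Four stronger readings are tempting, and the document does not support them:

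- *That the package is perfectly confounded with age composition.* The article never says that MAMG lacked T-shirts, gatherings or older leaders. Their absence is inferred from MAMG being regular YMCA classes and from these features being described only for the other arms.
- *That SASG versus SAMG is a clean test of gender composition.* Tailoring and instructor gender may differ between them.
- *That the mediation hypothesis fails.* Hypothesis 3 concerns the assigned conditions, and features that raise cohesion are part of those conditions, so it remains testable. Only a reading specific to similarity goes too far for the MAMG contrasts.
- *That perceived similarity by arm would settle the matter.* The identity-building features could themselves raise perceived similarity.

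**Conclusion.** The concern holds as a matter of interpretation. The statements in the Abstract and Discussion that a difference from MAMG supports changing group composition go beyond what the design can show. None of the three pairwise contrasts isolates age composition. One bears on gender composition, with the caveat about tailoring and instructor gender. How much of any MAMG difference is due to composition cannot be determined from the arm means, so no numerical size can be attached to the bias.

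The conclusion assumes that the package features were absent, or at least less present, in the MAMG classes, which is the natural reading of the article but is not stated in it. It does not imply that the trial is invalid: each arm can still be compared with usual YMCA classes as a whole programme.

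**What to change.** 1. In the Discussion paragraph of the Abstract and in the main Discussion, state that contrasts with MAMG estimate the effect of a multi-component, peer-led, age-restricted programme against usual YMCA classes. Remove or condition the wording that credits composition.
2. Rest any composition claim on SASG versus SAMG, describe it as concerning gender composition, and note that tailoring and instructor gender may also differ. Make no separate claim for age composition.
3. Add T-shirts, gatherings, peer leadership and purpose-built content to the limitations as alternative explanations for differences from MAMG, beside the class choice already listed.
4. Read mediation of the MAMG contrasts as mediation of the assigned programme, not of similarity alone.
5. Optionally, report by arm the perceived similarity collected at weeks 2 and 14, as description only, since it does not separate composition from the package.

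The cost is wording, plus one descriptive table if item 5 is taken up. The arms cannot be changed now: the first cohort is complete and the second is under way. Trial status reports that no data have been analysed, so the interpretation can still be fixed before results are known. The downside is a narrower headline claim.

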## Abbreviations

GOAL: GrOup-based physical Activity for oLder adults
MAMG: Mixed-Age Mixed-Gender
SAMG: Similar-Age Mixed-Gender
SASG: Similar-Age Same-Gender
PAR-Q+: The Physical Activity Readiness Questionnaire for Everyone
ePARmed-X: The Electronic Physical Activity Readiness Medical Examination
